### Randomisation

A patient will be randomised to the study once they have met the eligibility criteria. The randomisation of participants will occur via a central computer generated randomisation service—the Macquarie Clinical Trials Unit (who will not be involved in patient care, data collection or analysis). The day prior to surgery, the pharmacy will receive the randomisation code via email, allocating the patient to one of the two groups.

Due to expected differences in dissection technique, stratified randomisation will be performed based on the number of levels operated on (dichotomised to ≤2 or >2).

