## Methods

### Design

This is a protocol for a pragmatic, multi-centre, blinded, parallel-group, randomised controlled placebo trial. The trial is being conducted in two metropolitan academic hospitals in Sydney, Australia (Macquarie University Hospital and Nepean Public Hospital).

All patients will undergo general anaesthesia (GA). The patients randomised to the intervention group will have a SCPB administered under ultrasound guidance with a local anaesthetic solution, whilst patients randomised to the placebo group will be injected with a saline solution. All patients will be admitted to the high dependency unit (HDU) post-operatively, which is routine practice in the primary centre.

The primary endpoint is the QoR-40 score at 24 h after surgery. It will be measured by blinded assessors. A participant timeline can be found in Fig. 1.

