Intraoperatively, all patients will receive 4mg of intravenous (IV) dexamethasone after induction as prophylaxis for postoperative nausea and vomiting (PONV) and may prolong the duration of the block anaesthesia and before surgical incision. Approaching closure of the wound, patients will receive 1g of IV paracetamol followed by 4mg of IV ondansetron or 1mg or IV granisetron for PONV prophylaxis.

Additional analgesia will be provided with incremental boluses of opioids at the discretion of the anaesthetist. At the end of the surgery, maintenance of anaesthesia either sevoflurane or propofol and remifentanil will be turned off and the neuromuscular blockade will be reversed with neostigmine (50 mg/kg IV) and glycopyrrolate (10 mcg/kg IV) or sugammadex.

Patients will then be taken to the post-anaesthetic care unit and then to the HDU, or directly to the HDU. The general post-operative care of the patients will be directed by the local standard practice in terms of monitoring and assessment of neurological status, pain, PONV and level of sedation.

Patients will be asked to rate their pain upon arrival and at regular intervals using an 11 point Numerical Rating Scale by the recovery nurse (0 = no pain to 10 = the worst pain imaginable; D= difficult to assess, U= unconscious). This score is recorded separately when at rest and with patient movement. The character of pain will be recorded as one of five choices (dull, pressure, radiating, sharp, throbbing). Nausea and vomiting will be assessed using a scoring system (0= no nausea 1= occasional nausea, 3= nausea and occasional vomiting, 4= constant vomiting). The level of sedation will be recorded using an analogue score (0= wide awake, 1= easy to rouse, 2= drowsy, 3= difficult to rouse, 4= unrousable). To maintain a pain score of <4, or the patient being clinically comfortable, an opioid will be administered IV every 2 to 5 min as needed. The choice of opioids will be at the discretion of the anaesthetist.

Difficulty with postoperative nausea and vomiting will be treated with 0.5mg of IV droperidol and/or 4mg of IV Ondansetron. In the first post-operative day, patients will receive regular paracetamol (1g four times a day) and oral opiates or a patient controlled analgesia (PCA), at the discretion of the anaesthetist.

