### Statistical analysis

Baseline characteristics will be summarised by treatment group to assess comparability. We are not planning to adjust the analyses for baseline variables.

Data analysis will be performed according to the intention-to-treat principle. The primary outcome will be analysed by a comparison of scores using an independent t test, with 95% confidence intervals and two-tailed p values reported. Significance levels will be set at 0.05.

The 24-h opiate usage and hospital length of stay will by analyses using independent t tests with 95% confidence intervals and two-tailed p values reported.

Nausea and vomiting will be recorded as categorical variables and analysed using the Pearson chi-squared test.

For the analysis of pain scores across the four periods a linear regression analysis will be used with the dependent variable being the pain score and the independent variables being ‘period’, ‘group’ and ‘period*group’ interaction. This analysis will be conducted within the framework of Generalised Estimating Equations, which corrects the bias in the estimates of the SE caused by having multiple observations per person and thus correlation in the data. The output generated would be the difference between the groups across all periods (95% CI and p value) and the difference between the groups in each period (95% CI and p value).

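### Hospital enters neither the allocation nor the analysis of this two-hospital trial, which costs a little precision; it does not bias the result

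*Protocol article*

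**What the plan says.** The Randomisation section of the protocol article states that "stratified randomisation will be performed based on the number of levels operated on", split at two levels. The reason given is surgical: "Due to expected differences in dissection technique". Hospital is not named as a factor, although the Design section says "The trial is being conducted in two metropolitan academic hospitals in Sydney, Australia". Allocation comes from a central computer-generated service.

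The Statistical analysis section states "We are not planning to adjust the analyses for baseline variables". QoR-40, 24-hour opioid use and length of stay are compared by independent t tests, and nausea and vomiting by the Pearson chi-squared test. The pain model contains only period, group and their interaction.

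On care that could differ between hospitals, the Intervention section says "The general post-operative care of the patients will be directed by the local standard practice in terms of monitoring and assessment", and of opioids given for pain after surgery, "The choice of opioids will be at the discretion of the anaesthetist". The oral or patient-controlled route on the first day is also left to the anaesthetist. The Design section says "All patients will be admitted to the high dependency unit (HDU) post-operatively, which is routine practice in the primary centre".

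**The concern.** When a trial recruits at more than one hospital and outcomes differ between them, each arm's mean depends partly on how many of its patients come from each hospital. Stratifying by hospital fixes that mix by design, and a hospital term in the model removes its contribution to the error. This plan does neither, so the hospital mix is left to chance and the between-hospital variance stays in the standard error.

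What is at stake is precision. The sample size gives almost exactly 80% power, and the Discussion acknowledges that this could be regarded as low, so even a small avoidable loss is worth recovering. The same mechanism acts on opioid use, length of stay and pain if these differ between the hospitals.

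**Working it through.** **Inputs from the article.** Target difference 7.5 and SD 15 (Primary outcome); two-sided 5% test, power 0.80, 64 per group, 5% dropout, 136 randomised as 68 + 68 (Sample size calculation and Statistical analysis); 17 patients recruited (Trial status).

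**Assumed, because the article does not give them.** Share p of patients at the second hospital: 15% to 50%. Hospital gap D in mean QoR-40: 7.5 points, with 15 as an extreme. Within-hospital SD: 15.

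**1. The plan's own figure.** The noncentral t calculation with difference 7.5 and SD 15 gives power 0.801 at 64 per group and 0.795 at 63. Then 64 / 0.95 = 67.4, rounded up to 68 per group, or 136. The stated sample size reproduces.

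**2. Chance imbalance in hospital mix.** With K of 136 patients at the second hospital and 68 per arm, the number X in one arm is hypergeometric. The between-arm difference in share is (2X − K)/68, with

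SD = (2/68) × √[68 × (K/136) × (1 − K/136) × 68/135].

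| Second-hospital share | K | SD of difference (percentage points) | P(difference ≥ 10 points) |
|---|---|---|---|
| 15% | 20 | 6.1 | 0.088 |
| 20% | 27 | 6.9 | 0.197 |
| 30% | 41 | 7.9 | 0.262 |
| 50% | 68 | 8.6 | 0.230 |

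The last column does not rise steadily because the counts are discrete. The calculation assumes an exact 68:68 split and ignores the levels stratum.

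**3. Effect on the QoR-40 estimate.** Shift = difference in share × D. For D = 7.5 the 95% range is ±1.96 × 0.069 × 7.5 = ±1.0 points at a 20% share and ±1.96 × 0.086 × 7.5 = ±1.3 at 50%. For D = 15 it is ±2.0 and ±2.5. For comparison, the standard error of the treatment difference is 15 × √(2/64) = 2.65.

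**4. Effect on power.** Without a hospital term the SD becomes √[15² + p(1 − p)D²]. For D = 7.5:
- p = 0.2: √(225 + 9.0) = 15.30, power 0.786.
- p = 0.5: √(225 + 14.06) = 15.46, power 0.777.

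For D = 15 the SDs are 16.16 and 16.77, with power 0.741 and 0.709.

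**5. Simulation of the options** (128 evaluable patients, 100,000 runs per setting). Ranges cover shares of 20% and 50%.

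| Allocation / analysis | Type I error, D = 7.5 | Type I error, D = 15 | Power, D = 7.5 | Power, D = 15 |
|---|---|---|---|---|
| Not stratified by hospital, unadjusted (current plan) | 0.050-0.051 | 0.049-0.051 | 0.78-0.79 | 0.71-0.74 |
| Stratified, unadjusted | 0.044-0.045 | 0.028-0.034 | 0.78-0.79 | 0.73-0.76 |
| Stratified, hospital in model | 0.050-0.052 | 0.049-0.051 | 0.80 | 0.80 |
| Not stratified, hospital in model | 0.049-0.051 | 0.050 | 0.80 | 0.80 |

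The current plan is valid. Stratifying while keeping the unadjusted test recovers only about 0.5 to 2.5 points of power and makes the test conservative. The hospital term in the model does most of the work.

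**6. Sensitivity to the meaning of SD 15.** If 15 already includes the hospital variation, the plan has its stated power and the change is a gain. The within-hospital SD for D = 7.5 is then √(225 − 9.0) = 14.70 or √(225 − 14.06) = 14.52. By the normal approximation, power rises from 0.807 to 0.823 or 0.832. The size is similar either way.

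**The case against.** The strongest reply is that this is a defensible design choice. The authors give a reason for the factor they chose, few strata suit a 136-patient pragmatic trial, and chance imbalance in a prognostic factor is ordinary sampling error already reflected in the confidence interval. That stands: no test is invalid and no statement is contradicted.

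A reader might infer that the arms could be confounded by hospital and the comparisons biased. The documents do not support this. Randomisation makes the hospital mix equal in expectation, and the simulated type I error of the planned test stays at about 0.05.

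A reader might also infer that the article itself shows the hospitals treating patients differently, so that opioid use and length of stay follow local practice. It does not go that far. The sentence on local practice concerns monitoring and assessment; opioid choices belong to the individual anaesthetist and are not described as hospital policy; HDU admission applies to every trial patient; nothing ties discharge to local practice. Much else is common to both sites: two standard anaesthetic regimens, the block technique, antiemetic prophylaxis, regular paracetamol and a pain target. A hospital difference is plausible but not documented, and the gaps used above are assumptions. The 7.5-point gap equals the whole target difference, which is generous, and the loss shrinks if one hospital recruits most patients.

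What remains is that an inexpensive gain in precision is left unused.

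**Conclusion.** The point holds as a minor improvement. Number of levels is the only stated stratification factor, there are two hospitals, and the analyses are unadjusted, so any hospital difference in outcome adds avoidable noise. For an assumed 7.5-point QoR-40 gap and a 20% to 50% share at the second hospital, power is 0.78-0.79 instead of about 0.80; at an extreme 15-point gap it is 0.71-0.74. With no hospital difference nothing is lost. For opioid use and length of stay the direction is the same, but the article gives no SD or hospital difference from which to size it. The validity of the primary test and the stated sample size are unaffected.

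**What to change.** Two changes, made together:

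1. In Randomisation, add hospital as a second stratification factor in the central service for all remaining patients: 2 hospitals × 2 level groups = 4 strata. Existing allocations stand. With 17 recruited, 136 − 17 = 119 patients remain.
2. In Statistical analysis, replace the sentence ruling out adjustment with a statement that hospital and number of levels are covariates in the primary and secondary models: a linear model in place of each t test, an analysis of nausea and vomiting that takes account of both factors, and both terms added to the pain model.

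The second change should not be dropped. Stratifying alone leaves the t test conservative, whereas adjusting for hospital without stratifying already brings power to about 0.80. If the allocation cannot be changed, the covariates alone are worth having.

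The cost is a short amendment through the two ethics committees and the registry, a change of setting at the randomisation service, and possibly one sparse stratum among patients with more than two levels at the smaller hospital. The sample size does not change.

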### Concealment

The hospital pharmacy will produce the solution after receiving the randomisation notice and will send the blinded solution to theatre on the day of surgery in a vial marked “Ropivacaine 0.2% OR Placebo 15mL” along with the patient’s name, study enrolment number and expiry date.

### Blinding

The surgeon and anaesthetist will be blinded to the solution being injected. The surgeon performing the operation will follow-up with the patient 6 weeks later and will remain blinded to their study allocation. The patient will not be aware which solution they will be receiving and will remain blinded to the study arm they are allocated to after the operation. The investigators conducting the questionnaires will not be aware of the treatment given to the patient.

### Primary outcome

The primary outcome will be the QoR-40 score measured at 24 h post-operation completion time. The ‘quality of recovery’ score was developed to provide a patient-orientated assessment of the quality of recovery after surgery and anaesthesia [14]. This was later expanded to the QoR-40 score. This score was validated and shown to be reliable when completed on the first post-operative day [15]. The score measures five dimensions of patient experience: pain, emotional state, physical independence, comfort and psychological support. A systematic review showed that the QoR-40 was a widely used, valid, reliable and responsive tool for assessing quality of recovery from a patient perspective [16].

The minimum clinically important difference (MCID) can be thought of as the smallest change that is important to a patient and is an especially important concept in studies involving patient-reported outcomes [17]. There are various methods of determining MCID. A 2016 study, using the anchor method, determined the MCID to be 6.3 for the QoR-40 score [18]. Based on cardiac studies, one author argued that a change of 5–7 signifies a clinically important difference in the QoR-40 score [19]. A randomised study of patients undergoing cervical spine surgery predefined the MCID as a change of 10 [20]. In a prospective study of patients undergoing neurosurgery procedures, the mean QoR-40 at post-operative day 1 in 92 patients undergoing spinal surgery was 160 (SD-15) [21]. Based on the distribution-based approach of determining MCID (that is, half standard deviation), the MCID would be 7.5. Taking this into account, we chose a change of 7.5 to signify a clinically important change in a spinal surgery setting.

### Secondary outcomes

A 24-h opioid usage (converted to equivalent units of oral morphine).Numeric pain rating scale for neck pain at 1 h, 3 h, 6 h and at 24 h post-operative time.Incidence of nausea and vomiting, in the first 24 h after surgery.Hospital length of stay.

### Sample size calculation

The primary endpoint is the QoR-40 score at 24 h post-operatively, and thus, we are planning a study of a continuous response variable from independent control and experimental subjects with 1 control per group. We used an MCID of 7.5 for the QoR-40, as discussed above. If the true difference between the groups is 7.5, we will need a study of 64 subjects in each group to be able to reject the null hypothesis that the population means of the experimental and control groups are equal with probability (power) 0.8. The type 1 error associated with this test of the null hypothesis is 0.05.

Allowing for a dropout rate of 5%, we will randomise 136 patients (68 in each group). The software used to do the calculation was PS from the University of Vanderbilt, USA.

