## Discussion

Here, we present the protocol for a randomised controlled trial evaluating the role of SCPB in ACSS. The trial is unique as it is the first placebo trial and the first completely blinded trial of its nature. This protocol conforms to the Standard Protocol Items: Recommendations for Interventional Trials [22].

Whilst SCPB has been studied in thyroid and carotid surgery, there is a paucity of evidence for performing SCPB for ACSS. A single centre, non-blinded, randomised controlled trial (RCT) comparing GA to awake surgery with bilateral deep and superficial cervical plexus blocks found a trend towards better post-operative pain control in the cervical plexus block group. The GA group however had better intra-operative haemodynamic stability and patient satisfaction scores [23]. It has been shown that SCPB is preferred to deep cervical plexus block, as the deep block is associated with a greater risk profile without conferring a significant benefit [10].

The only trial we are aware of studying SCPB in ACSS is an RCT comparing unilateral SCPB with no block in patients undergoing single or two-level ACDF [20]. The primary outcome was the QoR-40 score measured at 24 h post-surgery. The patients were blinded, but the surgeon and anaesthetist were not. It was a single-centre study that enrolled 23 patients to each group. The QoR-40 scores were significantly better in the SCPB group (179 [116-195] vs. 157 [97-196]) (median [interquartile range]).

The disadvantages of this trial include the small number of patients, the lack of investigator blinding and the lack of a placebo. The chosen MCID of 10 points for the QoR-40 score is not reflective of the current literature (see above). In addition, we believe a bilateral SCBP yields superior outcomes to a unilateral block as the surgical incision can sometimes reach, or cross, the midline. Finally, the block was landmark-based, rather than ultrasound-guided. Ultrasound-guided SCPB has greater efficacy and reduced local anaesthetic toxicity compared to the landmark technique [24, 25]. The design of our proposed trial addresses each of these issues.

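### The 80% power for a 7.5-point difference holds only if the QoR-40 SD is about 15, a value the sample size section does not state and the quoted anterior cervical data do not support

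*Protocol article*

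**What the plan says.** The Sample size calculation section takes its target difference from the Primary outcome section ("We used an MCID of 7.5 for the QoR-40, as discussed above") and then states "If the true difference between the groups is 7.5, we will need a study of 64 subjects in each group". The power is given as 0.8 ("population means of the experimental and control groups are equal with probability (power) 0.8") and the type 1 error as 0.05. With 5% dropout the total is 136, or 68 per group. No SD is given in this section. The Statistical analysis section specifies the test: "using an independent t test, with 95% confidence intervals and two-tailed p values reported".

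The only SD in the protocol is under Primary outcome: "the mean QoR-40 at post-operative day 1 in 92 patients undergoing spinal surgery was 160 (SD-15". The same paragraph takes half of it: "Based on the distribution-based approach of determining MCID (that is, half standard deviation), the MCID would be 7.5".

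The Discussion quotes one trial of this block in anterior cervical surgery, with 23 patients per group and the same questionnaire at 24 h. Its scores are given as "179 [116-195] vs. 157 [97-196]) (median [interquartile range". The protocol does not compare that spread with SD 15. The Discussion acknowledges a possible type II error if the effect is smaller than predicted, but does not mention a larger SD.

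**The concern.** Power for a fixed 7.5-point difference depends directly on the SD. A reader of the power statement sees 0.8 with no SD attached and cannot tell that it is conditional. The value behind it comes from mixed spinal surgery, while the protocol's own figures for the operation under study show a much wider spread, whichever way the brackets are read.

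The Abstract and the Discussion both say that a result showing no benefit would make the block unnecessary. If the SD is well above 15, a real 7.5-point benefit would often be missed, and a non-significant result would not support that conclusion.

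**Working it through.** **Inputs.** Difference 7.5, alpha 0.05, power 0.8 and 64 per group (Sample size calculation); two-sided independent t test (Statistical analysis); SD 15 (Primary outcome); bracket limits 116 to 195 and 97 to 196, medians 179 and 157, 23 per group (Discussion).

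**1. Reproducing the plan.** Two-sided noncentral t, 126 degrees of freedom, SE = SD × √(2/64).
- At SD 15: SE = 15 × 0.1768 = 2.652, noncentrality 7.5/2.652 = 2.83, power 80.1%. With 63 per group it is 79.5%, so 64 is right.
- Solving for the SD that gives exactly 80% at 64 per group returns 15.03, so SD 15 is the input used.
- Dropout: 64/0.95 = 67.4, rounded up to 68 per group, 136 in all. This also reproduces.

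**2. Brackets read as labelled (interquartile ranges).** A lower bound on the SD needs no normality: put a quarter of the scores at each outer quartile, and one quarter on each side of the median, placed to make the variance as small as possible.
- Block arm: points 116, 163, 179, 195, mean 163.25, variance (47.25² + 0.25² + 15.75² + 31.75²)/4 = 872.2, SD 29.5.
- Control arm: points 97, 150, 157, 196, mean 150, variance (53² + 0² + 7² + 46²)/4 = 1243.5, SD 35.3.
- Power at 64 per group is at most 30% and 22% at these SDs.
- The usual normal conversion gives 79/1.349 = 58.6 and 99/1.349 = 73.4, with power of 11% and 9%. SDs of that size look implausible for this score, so the label itself is doubtful.

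**3. Brackets read as full ranges (assumption).** The expected range of 23 normal values is 3.858 SD.
- Block arm: 79/3.858 = 20.5, power 54%.
- Control arm: 99/3.858 = 25.7, power 37%.
- Pooled: √((20.5² + 25.7²)/2) = 23.2, power 44%.

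**4. Could SD 15 still produce such ranges?** The two arms' average range is (79 + 99)/2 = 89. By simulation with a true SD of 15 and 23 per arm, an average range of 89 or more occurs about 0.02% of the time with normal scores and about 2% with strongly skewed (exponential) scores. Under normality the average range gives an SD of about 23, with a 95% interval of about 18 to 30. The block arm alone is compatible with an SD as low as 14.6.

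**5. What the SD does at 64 per group.** Half-width = 1.979 × SE.

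| SD | Power for 7.5 | 95% CI half-width |
|---|---|---|
| 15 | 80% | 5.2 |
| 20 | 56% | 7.0 |
| 25 | 39% | 8.7 |

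At SD 15, the interval excludes a 7.5-point benefit when the observed benefit is below about 7.5 − 5.2 = 2.3 points. At SD 20 it must be below about 0.5. At SD 25 even an observed difference of zero would not exclude 7.5.

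**The case against.** The strongest reply is that nothing has been miscalculated. The sample size section refers back to the Primary outcome section, which gives SD 15 and its source, and a directly reported SD from 92 spinal patients is a reasonable planning figure beside a back-calculation from 23 per arm. This stands as far as the arithmetic goes. It does not justify a power statement that omits the SD and ignores contrary figures in the same document.

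A reader might infer that the protocol's own data show power to be 37% to 54%. They do not. That range needs the brackets to be minimum and maximum values, which is not how the protocol labels them. Only the cited trial can settle the label.

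A reader might also infer that SD 15 is contradicted. That is too strong under the range reading. A range depends on two patients per arm, and the block arm's median lies close to its upper limit, which suggests skew. With the printed minimum, median and maximum, a sample of 23 could have an SD as low as about 13.6 (block) or 15.2 (control), though only if nearly all patients scored at or near the median.

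Nor do the documents support calling 7.5 circular. The half-SD rule fixes the standardised effect at 0.5, so 64 follows whatever the SD. But the protocol also sets 7.5 beside published values of 6.3, 5–7 and 10.

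Finally, the earlier trial's medians differ by 22 points. If the true mean difference were that large (an assumption), power at SD 25.7 would exceed 99%. That is fair, but the protocol's claim is about 7.5 points, and the low power figures apply to that difference only.

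**Conclusion.** The point holds as a fault in the SD assumption, not in the calculation. The stated 0.8 is conditional on an SD of about 15, and the only same-surgery figures quoted are hard to reconcile with that value. Power for 7.5 points is at most about 22% to 30% if the brackets are interquartile ranges, and about 37% to 54% if they are full ranges.

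The first pair takes the printed quartiles at face value, although they come from 23 patients per arm. The second rests on an unconfirmed reading and a normal conversion from ranges. The true SD in this trial is unknown, and the documents do not establish any single power figure in place of 80%. They do show that an unconditional 0.8 is not supported, and that a non-significant result could not by itself show the block to be unnecessary.

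**What to change.** - Check the label on the bracketed scores in the Discussion against the cited trial, and correct it if needed.
- In the Sample size calculation section, state SD 15 and its source, and replace the unconditional 0.8 with power at 64 per group for SD 15, 20 and 25 (80%, 56%, 39%) and the matching CI half-widths (about 5.2, 7.0 and 8.7 points).
- Add one blinded check of the SD, computed over both groups together at a pre-set number of patients, and restate the detectable difference from it. Ignoring allocation inflates the SD only slightly: with a true 7.5-point difference and SD 15 it gives √(225 + 7.5²/4) = 15.5.
- In the Abstract and the Discussion, make any conclusion that the block is unnecessary depend on the 95% CI excluding a 7.5-point benefit.

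The cost is wording, one blinded calculation and a less favourable stated power. Allocation stays concealed, no test of the treatment effect is made, and enrolment does not change. These steps disclose a shortfall and do not remove it. For scale, 80% power would need about 112 evaluable patients per group at SD 20 and 175 at SD 25, from 2 × (1.96 + 0.84)² × SD²/7.5². Seventeen patients had been recruited when the article was written, so the change could be made early.
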